# Effects of Elastic Tape Associated With Pulmonary Rehabilitation in Male Individuals With Chronic Obstructive Pulmonary Disease: Protocol for a 2-Arm, Assessor-Blinded Randomized Controlled Trial

**DOI:** 10.2196/75029

**Published:** 2026-02-27

**Keywords:** chronic obstructive pulmonary disease, COPD, adhesive elastic tape, pulmonary rehabilitation, dyspnea, exercise capacity, physical capacity

## Abstract

**Background:**

Individuals with severe chronic obstructive pulmonary disease (COPD) may exhibit thoracoabdominal asynchrony, which reduces ventilatory efficiency. A novel intervention using elastic tape (ET) applied to the chest wall has been shown to acutely reduce thoracoabdominal asynchrony and dyspnea during exercise among individuals with COPD. We hypothesize that using ET in pulmonary rehabilitation (PR) may increase the benefits of PR in this population.

**Objective:**

This study aims to evaluate the additional effects of ET on exercise capacity, symptoms of anxiety and depression, health-related quality of life, and physical activity in daily life among male individuals with moderate to very severe COPD who are undergoing PR.

**Methods:**

This is a protocol for a randomized, controlled, 2-arm, parallel, blinded assessor clinical trial. Individuals will be followed for 8 weeks, twice a week, with PR sessions lasting approximately 1 hour. Health status (COPD Assessment Test), health-related quality of life (Chronic Respiratory Questionnaire), and psychological distress (Hospital Anxiety and Depression Scale) will be assessed before and after the intervention. Then, exercise capacity will be assessed via the incremental shuttle walking test and endurance shuttle walking test, and participants will use a triaxial accelerometer (ActiGraph) for 7 days to assess physical activity in daily life. Subsequently, individuals will be randomized into ET or sham groups; both groups will complete a PR program (2 times per week for 8 weeks). The ET group will receive applications of ET, whereas the sham group will receive a nonelastic tape. Data will be presented as means and SDs or medians and IQRs. Intergroup comparisons will be performed using a 2-way ANOVA, followed by the Bonferroni post hoc correction test, or the Kruskal-Wallis test, followed by the Dunn post hoc test. The threshold for statistical significance will be set at 5%.

**Results:**

The clinical trial registration was approved in June 2023. Recruitment and data collection for the trial are ongoing; as of November 2025, a total of 10 individuals have been recruited, and the results are expected to be available by the end of November 2026.

**Conclusions:**

We hypothesize that the use of ET can enhance the benefits of PR in individuals with moderate to very severe COPD and increase exercise capacity and quality of life, as well as reduce symptoms of anxiety and depression.

## Introduction

Chronic obstructive pulmonary disease (COPD) is a preventable and treatable disease characterized by persistent and progressive airflow limitations associated with a chronic inflammatory response of the airways [1]. In the PLATINO (Projeto Latino-Americano de Investigação em Obstrução Pulmonar) study conducted in 2005, the prevalence of COPD was 15.8% (95% CI 13.5%‐18.1%) using the fixed ratio definition. COPD showed a positive association with age and smoking and an inverse association with BMI; thus, we understand that most individuals with COPD in the Brazilian population are not obese [2]. These findings were consistent with a study published in 2019 [3], which showed that individuals with moderate to very severe COPD had a slight reduction in BMI. The same 2019 study [3] showed that there was a similar prevalence for both sexes. Individuals with COPD experience destruction of the small airways and decreased elastic recoil, leading to air trapping at rest due to the loss of the intrinsic tendency of the lungs to deflate. Movements of the thoracic and abdominal compartments may be impaired and may become worse with exertion [4]. Therefore, the rib cage and abdomen may move uncoordinately; this phenomenon is called thoracoabdominal asynchrony (TAA) [5].

TAA occurs in individuals with severe airway obstruction, leading to a mechanical disadvantage, increased breathing work, dyspnea symptoms, limited exercise, and reduced physical activity in daily life (PADL) [6,7]. To our knowledge, few studies have found interventions to minimize TAA. Yamaguti et al [8] found that a diaphragmatic breathing retraining program could reduce TAA among individuals with COPD. Recently, Pinto et al [9] accomplished a novel intervention using elastic tape (ET) in the chest wall and demonstrated that ET reduces TAA, tidal volume, minute volume, and dyspnea during isoload exercise among individuals with severe to very severe COPD. Individuals also demonstrated improvements in maximal oxygen consumption during cardiopulmonary exercise testing and a reduction in sedentary time during daily life. More recently, Santos et al [10] used ET for 3 weeks in patients with moderate to very severe COPD and reported reduced dyspnea symptoms as well as improved health status and health-related quality of life (HRQoL). Although these studies used ET, neither did so in conjunction with pulmonary rehabilitation (PR), and both studies had an intervention exposure duration of a maximum of 21 days. Furthermore, there is no evidence of ET being used in PR as an adjuvant strategy.

PR is an effective and successful treatment for individuals with persistent symptoms and/or excessive use of health care resources [11]. The European Respiratory Society and the American Thoracic Society define PR as a comprehensive intervention based on a thorough patient assessment followed by patient-tailored therapies, which include but are not limited to exercise training, education, and behavior changes designed to improve the physical and psychological conditions of people with chronic respiratory disease and to promote long-term adherence to health-enhancing behaviors [12,13]. The core of PR is exercise training, which directly addresses deconditioning and its association with decreases in symptoms such as dyspnea and fatigue, which are the primary reasons for referral. Exercise training programs also have additional positive effects on comorbidities, HRQoL, and general health [13]. However, the additional effects of ET associated with PR have not been studied.

Although previous studies have investigated the use of ET in isolation [9,10], and considering that ET has been shown to reduce TAA [9], our hypothesis is that the application of ET during a PR program may confer additional positive effects in individuals with greater disease severity regarding exercise capacity, symptoms of anxiety and depression, and HRQoL in individuals with moderate to very severe COPD undergoing PR.

## Methods

### Study Design and Participants

This is a protocol for a randomized, controlled, 2-arm, parallel, assessor-blinded clinical trial. Individuals with COPD will be screened and recruited at the pulmonology outpatient clinic of a tertiary hospital. The study protocol was developed in accordance with the SPIRIT (Standard Protocol Items: Recommendations for Interventional Trials) checklist guidelines.

### Analysis of the Population

The inclusion criteria will be as follows: diagnosis of moderate to very severe COPD [1], clinical stability (ie, no exacerbations for at least 30 days), male sex, nonobese status (BMI ≤29.9 kg/m^2^), absence of musculoskeletal limitations, and no participation in another research protocol or a PR program in the past 6 months. The exclusion criteria will be decompensated cognitive, neurological, and/or cardiological dysfunction and receiving home oxygen therapy. An intention-to-treat analysis will be performed using the patient’s most recent assessment in case of study dropout or absence of data and will be treated by imputing the last observation carried forward [14].

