### Experimental Design

Clinical and anthropometric data will be collected during the participant interview. Participants will complete questionnaires to assess health status (COPD Assessment Test [CAT]), HRQoL (Chronic Respiratory Questionnaire [CRQ]), and anxiety and depression symptoms (Hospital Anxiety and Depression Scale [HADS]). Then, a complete pulmonary function test (body plethysmography), the incremental shuttle walking test (ISWT), and the endurance shuttle walking test (ESWT) will be carried out. Finally, individuals will use a triaxial accelerometer (ActiGraph GT9X) for 7 days to assess their PADL. Lastly, individuals will be randomly assigned to 1 of 2 groups: the ET group or the sham group.

At baseline and postintervention, assessments will be performed by a researcher who is not involved in individual recruitment or intervention. After inclusion, individuals will begin an 8-week PR program twice a week (Figure 1). Individuals in the ET group will have the ET placed before the beginning of the PR program, and the ET will be replaced every 7 days throughout the 8-week period. The sham group will receive a nonelastic tape of the same color and size at the same position in the chest wall at the beginning of the PR program, and the tape will be replaced every 7 days, similar to the ET group. At the end of the PR program, participants will repeat the same assessments, except for the ISWT. The ESWT will be performed at the same level established by the ISWT during the initial evaluation (Figure 2).

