**Figure 2. F2:**
[figure not shown]
Schematic representation of the study design. Assessments were performed at baseline and after 8 weeks of intervention. 1RM: 1 repetition maximum test; CAT: COPD Assessment Test; CRQ: Chronic Respiratory Questionnaire; ET: elastic tape; ESWT: endurance shuttle walking test; HADS: Hospital Anxiety and Depression Scale; ISWT: incremental shuttle walking test; PAL: physical activity level; PR: pulmonary rehabilitation; PFT: pulmonary function test; V: visit.

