#### Sample Calculation

The sample size calculation was based on the primary outcome, based on a previous study showing a mean difference of 65 (SD 65) seconds between groups in the ESWT [29]. Thus, considering an alpha of .05 and a beta of .80, the estimated sample size will be 17 individuals per group. To account for potential losses and to allow for data imputation under the intention-to-treat principle, the sample size was increased by 20% in each group. Therefore, the final estimated sample size was 21 participants per group.

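### With one post-baseline assessment, last observation carried forward gives every dropout zero change, diluting the tape effect and undercutting the 20% sample-size allowance

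*Protocol article*

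**What the plan says.** The Analysis of the Population section promises an intention-to-treat analysis that uses each patient's latest available assessment "in case of study dropout or absence of data and will be treated by imputing the last observation carried forward".

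The visit schedule has two time points. The Figure 2 caption states: "Assessments were performed at baseline and after 8 weeks of intervention". Experimental Design adds: "At the end of the PR program, participants will repeat the same assessments, except for the ISWT". The endurance shuttle walking test (ESWT) is therefore measured once before and once after the programme.

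The Sample Calculation section rests on a previous study "showing a mean difference of 65 (SD 65) seconds between groups in the ESWT" and continues: "considering an alpha of .05 and a beta of .80, the estimated sample size will be 17 individuals per group". For losses, and "to allow for data imputation under the intention-to-treat principle", "the sample size was increased by 20% in each group", which gives 21 per group.

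Statistical Analysis names a two-way repeated-measures ANOVA, with a rank test if assumptions fail, and repeats the intention-to-treat principle. The PR Program section, however, makes at least 80% attendance (13 sessions) a condition for analysis of the results. No other missing-data method and no sensitivity analysis is stated.

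**The concern.** Carrying the last observation forward presumes some later observation to carry. Here there is none between baseline and the final visit, so the rule becomes baseline carried forward, and a patient who misses week 8 is analysed with a change of exactly 0 s. That is an odd value in a trial where both arms train for 8 weeks and the Introduction and Discussion describe rehabilitation as effective and known to raise exercise capacity. Someone who attended most sessions but missed the last visit would count as having gained nothing.

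Three things are at stake: the size of the estimated tape effect, the power of a small trial, and, if the arms lose different numbers, the direction of the comparison. The extra patients recruited to cover losses may also not do the job that the Sample Calculation section gives them.

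**Working it through.** **Inputs from the documents.** Difference 65 s; SD 65 s; alpha 0.05; the stated beta of .80 read as 80% power; 17 per group, raised by 20% to 21; assessments at baseline and week 8 only.

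**Assumptions.** The SD of 65 s is the SD of individual change (the document does not say). The test is two-sided. Dropout is unrelated to outcome. The common rehabilitation gain g, meaning the sham-arm change in ESWT, is not given anywhere, so a range of 0 to 200 s is shown.

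**1. The plan's own figure.** The standardised difference is 65/65 = 1.0. A two-sided t test at 80% power needs 16.7 per group, so 17. Then 17 × 1.20 = 20.4, so 21. Both figures reproduce. With 17 observed per group, power is 0.81.

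**2. Equal dropout, fraction d in each arm.** With two time points, the group-by-time test of the planned ANOVA is a t test on change. Completers change by g (sham) or g + 65 (elastic tape); dropouts are set to 0.

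- Expected difference: (1 − d)(g + 65) − (1 − d)g = (1 − d) × 65. At d = 0.20 this is 0.8 × 65 = 52 s, whatever g is.
- Variance per arm: (1 − d) × 65² + d(1 − d) × m², where m is that arm's mean change. The second term comes from mixing zeros with real gains.
- Standard error: √[(V_tape + V_sham)/21].

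At g = 65 s: V_tape = 0.8 × 4225 + 0.16 × 130² = 6084; V_sham = 0.8 × 4225 + 0.16 × 65² = 4056; SE = √(10140/21) = 21.97 s; 52/21.97 = 2.37. Normal-approximation power is 0.66.

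| Gain g (s) | V_tape | V_sham | SE (s) | Power, normal approximation | Power, simulated t test |
|---|---|---|---|---|---|
| 0 | 4056 | 3380 | 18.82 | 0.79 | 0.77 |
| 65 | 6084 | 4056 | 21.97 | 0.66 | 0.64 |
| 100 | 7736 | 4980 | 24.61 | 0.56 | 0.53 |
| 150 | 10776 | 6980 | 29.08 | 0.43 | 0.41 |
| 200 | 14616 | 9780 | 34.08 | 0.33 | 0.32 |

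These simulated figures let each patient drop out at random with probability 0.20. With exactly 4 of 21 lost per arm they are 0.79, 0.67, 0.56, 0.36 and 0.18. With exactly 2 of 21 lost per arm they are 0.85, 0.79, 0.75, 0.64 and 0.51.

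**3. Equal dropout, no true effect.** The expected difference is (1 − d)g − (1 − d)g = 0. Simulated type I error is 0.05 with random 20% loss, and at or below 0.05 with 4 fixed losses per arm.

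**4. Unequal dropout, no true effect.** Bias = (0.75 − 0.90) × g = −0.15g for an assumed 25% loss in the tape arm and 10% in sham: −9.75 s at g = 65, −15 s at 100 and −30 s at 200. Simulated type I error runs from 0.08 at a 65 s gain to 0.17 at 200 s. Reversing the split reverses the sign. With fixed losses of 6 v 2 of 21, the bias is −(4/21)g, or about −12, −19 and −38 s, and type I error is 0.08 to 0.12.

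**The case against.** **The power loss rests on figures that the document does not give.** This stands. A reader might infer that the rule destroys the planned power, but with no rehabilitation gain the loss is only a few points, and with 2 lost per arm and a 65 s gain power is still 0.79. The worst figure needs a gain of about three SDs (200/65 = 3.1) with no extra spread. The plan would also move to a rank test if assumptions fail; at a 200 s gain a rank test on change has power of about 0.47, not 0.32. That is still well below 0.80.

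**Dropout need not bias the comparison.** This stands too. A reader might infer bias without condition, but equal dropout only pulls a true effect toward zero. False positives need unequal loss. The document gives no rate or direction: both arms wear adhesive tape, and the skin check and removal rule apply to both. Unequal loss remains plausible, because the tapes differ in material and tension and an unresolved skin reaction ends participation. In arms of 21, a gap of a few dropouts can also arise by chance.

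**The standard error is not shown to be wrong.** Treating imputed values as observed is a weakness in principle, but the test keeps its 5% level under equal dropout, so understated error is not demonstrated here.

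**Perhaps dropouts really gain nothing.** Then 52 s is the effect among all randomised, and a missing-at-random analysis would overstate it. The document cannot settle this. It does not, however, state such an aim, and power at 21 per group would be just as low.

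**The attendance condition may exclude dropouts instead.** If it governs, most dropouts are never imputed and much of the power loss does not arise. But that contradicts the two intention-to-treat statements, so it is a further defect and not a defence.

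**Conclusion.** The concern holds in conditional form. It is certain from the text that the stated rule amounts to baseline carried forward, with zero change for every dropout. If dropouts would otherwise have benefited like completers, equal dropout dilutes the effect by the dropout fraction: 65 s becomes 52 s at the plan's own 20% allowance. At that loss, power falls below the planned 80% by an amount that depends on the unstated rehabilitation gain, from 0.77 at no gain to 0.32 at 200 s, taking 65 s as the SD of change. Analysing the 17 completers per group alone would give 0.81, so raising the sample to 21 does not protect power under this imputation rule.

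False-positive bias arises only if dropout differs between arms, and its size here rests on assumed rates. The documents do not support saying that the comparison is biased whatever the dropout, that power is certainly lost on a large scale, or that the standard error is wrong. Confidence is high for the mechanism and limited for the magnitude. Because the rule acts directly on the primary comparison, it should be changed before analysis.

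**What to change.** 1. Make the primary analysis a baseline-adjusted ANCOVA, or a constrained mixed model, on all observed week-8 ESWT values from all randomised participants. Multiple imputation using arm, baseline ESWT, lung function and sessions attended is an alternative.
2. Keep baseline carried forward as a sensitivity analysis, and add a delta or tipping-point analysis in which dropouts do worse than completers by stated amounts.
3. Reconcile the 80%-attendance condition in PR Program with the intention-to-treat statements in Analysis of the Population and Statistical Analysis, so that it is clear whether low attenders and dropouts are analysed, imputed or excluded.
4. Reword the reason given for the 20% increase: it replaces lost completers and does not make carried-forward values informative.

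The cost is revised wording and statistical software that fits the chosen model. Recruitment was still under way, with 10 participants as of November 2025, so the change can precede analysis. The downside is that the primary result then relies on a missing-at-random assumption, which the sensitivity analyses probe. The team should also state which effect it wants to estimate for those who stop, since changing the method changes that too.

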### Ethical Considerations

Patients will be recruited from the pulmonology outpatient clinic of the Hospital das Clínicas de São Paulo, São Paulo, Brazil, and will be included in the study after signing the informed consent form. This study will be performed in accordance with the Declaration of Helsinki. The study was registered at ClinicalTrials.gov (NCT05939999), and the Hospital Research Ethics Committee approved the study (55617321.2.0000.0068). All participants will be informed about the possibility of withdrawing at any time without incurring any loss of treatment at the institution. Participants will receive an identification code according to the order of inclusion in the study. The data will be deidentified by excluding the main identifying elements such as name, address, date of birth, phone number, email, medical record number, institutional identification number, and social security number. In addition, participants will be informed about the voluntary nature of their participation; this means that there will be no compensation of any kind for participation.

### Randomization and Allocation Concealment

The randomization will be generated using a computer (Sealed Envelope [15]). An investigator who is not involved in patient recruitment, assessment, or intervention will perform group allocation. Group allocation will be concealed via consecutively numbered, sealed, opaque envelopes. After randomization, both groups (ET vs sham) will not be informed of their allocation, and the same instructions on perception of tape use will be given to both groups.

### Adverse Events

The individual’s skin condition will be assessed at every session during the PR program to immediately identify any allergic reactions to the tape in both groups. If any skin changes are identified, such as redness or itching, the tape will be removed immediately and will not be reapplied until the condition has been completely resolved. If the condition does not resolve within 72 hours, even after removing the tape, the individual will be referred for evaluation by a dermatologist and will be removed from the study.

### Experimental Design

Clinical and anthropometric data will be collected during the participant interview. Participants will complete questionnaires to assess health status (COPD Assessment Test [CAT]), HRQoL (Chronic Respiratory Questionnaire [CRQ]), and anxiety and depression symptoms (Hospital Anxiety and Depression Scale [HADS]). Then, a complete pulmonary function test (body plethysmography), the incremental shuttle walking test (ISWT), and the endurance shuttle walking test (ESWT) will be carried out. Finally, individuals will use a triaxial accelerometer (ActiGraph GT9X) for 7 days to assess their PADL. Lastly, individuals will be randomly assigned to 1 of 2 groups: the ET group or the sham group.

At baseline and postintervention, assessments will be performed by a researcher who is not involved in individual recruitment or intervention. After inclusion, individuals will begin an 8-week PR program twice a week (Figure 1). Individuals in the ET group will have the ET placed before the beginning of the PR program, and the ET will be replaced every 7 days throughout the 8-week period. The sham group will receive a nonelastic tape of the same color and size at the same position in the chest wall at the beginning of the PR program, and the tape will be replaced every 7 days, similar to the ET group. At the end of the PR program, participants will repeat the same assessments, except for the ISWT. The ESWT will be performed at the same level established by the ISWT during the initial evaluation (Figure 2).

**Figure 1. F1:**
[figure not shown]
CONSORT (Consolidated Standards of Reporting Trials) 2025 flow diagram showing the enrollment, allocation, follow-up, and analysis phases of the randomized controlled trial. Participants were assessed for eligibility, randomized into 2 groups—elastic tape+pulmonary rehabilitation (intervention group [IG]) or pulmonary rehabilitation alone (control group [CG])—and reevaluated after 8 weeks. The number of patients shown in the figure is the planned number based on the sample size. Outcome assessments included the Hospital Anxiety and Depression Scale (HADS), Chronic Respiratory Questionnaire (CRQ), and COPD Assessment Test (CAT). ESWT: endurance shuttle walking test; ISWT: incremental shuttle walking test.

